## Objectives, specific aims & rationale

### Objectives:

To longitudinally examine the prescribing patterns and predictors of OACs prescribing and to evaluate the clinical outcomes of the under prescription of OACs in NVAF patients.

### Specific aims:

1. To determine the incidence of NVAF diagnosis in England from the year 2009 to 2019.
2. To determine the proportions of patients with NVAF and those with NVAF and cancer who were prescribed OACs, antiplatelet alone or no treatment.
3. To examine the temporal trends of prescribing different types of OACs (i.e. VKAs and NOACs), and assess the factors associated with not prescribing OACs including patient demographics, socioeconomic status, history of cancer and other comorbidities, stroke and bleeding risk.
4. To assess the effect of OACs prescribing vs. no OACs on the clinical outcomes (stroke, bleeding, and death) in a comparative cohort of NVAF patients eligible for anticoagulation after controlling for patients' comorbid conditions, frailty, age, and antiplatelets use.
5. To assess the rate of clinical outcomes (i.e. bleeding recurrence, stroke, and mortality) after MB events and how they relate to OACs resumption and the timing of restarting OACs after the MB event.
6. To explore the variability across patient groups regarding OACs resumption after MB events and whether patients have continued on the same OAC before the MB event, switched to another OACs or received lone antiplatelet therapy.
7. To assess and compare patients' risk for stroke and bleeding recurrence using HAS-BLED, CHA2DS2-VASC, HEMORR?HAGES and GARFIELD-AF risk assessment scores, at the time of the indexed major bleeding event.

### Rationale:

Achieving these specific aims will allow the identification of predictors for the under prescription of OACs in NVAF who are eligible for anticoagulation therapy. By further comparing the clinical outcomes between OACs treated and not treated individuals we will be able to determine the characteristics of patients who are still more likely to benefit from receiving anticoagulation therapy. The outcomes of restarting OACs after major bleeding events and their associated benefits or risks are still not well known and the proper timing of restarting OACs after major bleeding events is still not certain and further studies are needed to evaluate the effect of different time intervals to resume OACs. Moreover, available risk assessment scores such as the HAS-BLED, CHA2DS2-VASC, and HEMORR?HAGES are used to assess patients' risk for stroke and bleeding when initiating OACs, but it is unclear if these scores or the new GARFIELD-AF score could be used to inform decision-making for restarting OACs after major bleeding events.

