**Methods and Data analysis:**

The study comprises of three phases; first an epidemiological study that aims to delineate incidence of NVAF from the CPRD GOLD and Aurum databases between 2009 and 2019. Prescribing of OACs will be assessed for all patients with NVAF and in a sub-group with cancer diagnosis and relevant data will be extracted to identify potential predictors of OACs prescribing and further assessment using multivariable logistic-regression modelling. The second phase will be a comparative cohort study of incident NVAF patients who were classified as "OAC not prescribed" in phase one, by using a propensity score matching method to match each patient not prescribed OACs to up to 5 comparable patients treated with OACs. Then we aim to compare stroke, bleeding, and all-cause mortality associated with OACs prescribing versus no OACs. The third phase will focus on patients who developed major bleeding events in phase two while taking OACs. We aim to explore the variability of OACs prescribing after bleeding across patient groups and the different predictors for OACs resumption. We will explore the rate of bleeding reoccurrence, stroke, and mortality, and how they relate to OACs prescribing and timing of restarting OACs. We will assess and compare patients' risk for stroke and bleeding reoccurrence after the bleeding event using different risk-assessment scores.

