**Covariates:**

- Patients' demographic information (age, gender, ethnicity, body mass index (BMI), geographic location (rural vs. urban), smoking status, alcohol consumption, Charlson comorbidity index for the severity of comorbidity (Appendix 4), electronic frailty index (eFI), and the index of multiple deprivation (IMD).
- For the sub-group of patients with NVAf and history of cancer, cancer diagnosis will be assessed at the index date of NVAf diagnosis and classified by cancer type into breast, prostate, colorectal, haematological, lung, and other types, and by cancer metastasis status.
- Drugs that affect either stroke or bleeding, or commonly interact with OACs, such as antihypertensive drugs, statins, antiarrhythmics, antidiabetic drugs, anticonvulsants, non-steroidal

anti-inflammatory drugs, corticosteroids, systemic azoles, HIV protease inhibitors and ciclosporin. (Appendix 2).

- The CHA2DS2-VASc stroke risk score that consists of 9 points, one for each of: congestive heart failure (CHF), hypertension (HTN), age  $\geq 75$  years (x 2 points), diabetes mellitus (DM), prior stroke or transient ischemic attack (TIA) or thromboembolism (x 2 points), vascular disease, age 65 to 74 years, and sex category. Information included in the CHA2DS2-VASc score will be identified using Read codes (Appendix 3 and 4), except for age and sex, to build the score and assess the risk of stroke for all included patients in the cohort. Further categorization of eligibility for OACs will be carried according to individual CHA2DS2-VASc scores; “not eligible for OAC” if CHA2DS2-VASc score = 0 in males, or 1 in females; and “OAC eligible” if CHA2DS2-VASc score  $\geq 1$  in males, or  $\geq 2$  in females.

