## **Data/statistical analysis**

1. Phase 1 - NVAF cohort: Annual and crude incidence rates of NVAF cases will be calculated and expressed as person-time at risk with 95% confidence intervals (95% CI). Incidence rates will be calculated by dividing the number of new diagnosed NVAF cases each year by the total population at risk during the same year. NVAF incidence in each calendar year of the study period (2009-2018) will be stratified by age and further standardized by age and deprivation quantiles. Status of anticoagulation therapy will be classified as either OAC prescribed or OAC not prescribed. OAC prescribed patients are those who received prescriptions for OACs during the study period. Treatment patterns for OAC users will be evaluated for OACs continuation, discontinuation or switched). OACs not prescribed will be defined as no prescription record of an OACs at any time after NVAF diagnosis, this will also include patients prescribed lone antiplatelet therapy. Proportions of patients prescribed antiplatelets will be described for both OACs prescribed and not prescribed patients. Baseline demographic, and clinical characteristics, and status of cancer diagnosis across OACs prescribed and not prescribed groups will be presented as number and percentage, mean $\pm$  (SD), or median (interquartile range), as appropriate. For both groups' eligibility for OACs will be described and categorized based on stroke risk according to CHA2DS2-VASc score. Trends in OACs initiation, switching from antiplatelet only to OACs, and from VKA to NOAC will be explored for each year and further stratified by eligibility for OACs and deprivation quantiles. To identify variables independently associated with OACs prescribing multivariate logistic regression models will be used and fitted with the covariates described in section N. Similarly, in a separate analysis for patients with NVAF and previously diagnosed cancer multivariate logistic regression models will be fitted to explore variables independently associated with OACs prescribing (i.e, cancer types and metastasis status). The level of statistical significance was set at  $P < 0.05$ .

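### The rationale promises predictors of under-prescription in OAC-eligible patients, but the Phase 1 prescribing models carry no eligibility restriction

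*Protocol*

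**What the plan says.** **Question posed.** The Rationale says the aims will allow "identification of predictors for the under prescription of OACs in NVAF who are eligible for anticoagulation therapy".

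**Eligibility rule.** Under Exposures, outcomes and covariates (Phase 1, Covariates), "Further categorization of eligibility for OACs will be carried according to individual CHA2DS2-VASc scores". Patients with "CHA2DS2-VASc score = 0 in males, or 1 in females" are classed as not eligible, and everyone with a higher score as eligible.

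**Population analysed.** The Technical Summary (Methods and Data analysis) states: "Prescribing of OACs will be assessed for all patients with NVAF and in a sub-group with cancer diagnosis". Candidate predictors are taken from there into multivariable logistic regression.

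**Models.** Data/statistical analysis, item 1, states: "To identify variables independently associated with OACs prescribing multivariate logistic regression models will be used and fitted with the covariates described in section N". No eligibility restriction is attached. The only separately defined model is for cancer: "in a separate analysis for patients with NVAF and previously diagnosed cancer multivariate logistic regression models will be fitted". It has no eligibility restriction either.

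**Stated uses of eligibility.** In the same item there are two. For both prescribing groups, "eligibility for OACs will be described and categorized based on stroke risk according to CHA2DS2-VASc score"; and yearly trends in initiation and switching are "further stratified by eligibility for OACs and deprivation quantiles".

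**Outcome.** OAC not prescribed means no OAC record at any time after diagnosis, whatever the patient's eligibility.

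**The concern.** Under-prescription means that a patient who should be considered for an OAC does not receive one. For a patient the protocol itself classes as not eligible, the absence of an OAC is the expected choice. The planned outcome nevertheless gives both patients the same code.

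This matters because eligibility is built from the same variables that the model examines. If uptake is lower in ineligible patients, each eligibility-defining factor is associated with prescribing by construction. A reader who takes the Rationale at its word would read those associations as reasons why eligible patients are or are not treated. The count in Feasibility counts is at least 120,000 incident cases and the analysis applies P<0.05, so even modest artefacts would be declared significant.

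**Working it through.** The documents state no figure for the Phase 1 model, so there is none to reproduce. The check has a textual part and a numerical part, and every numerical input below is an assumption.

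**1. Texts side by side.**

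| Place | Population |
|---|---|
| Rationale | NVAF patients eligible for OAC |
| Objectives; Specific aims, item 3 | NVAF patients, no eligibility limit |
| Technical Summary, Methods | all NVAF, plus a cancer sub-group |
| Data/statistical analysis, item 1 | no restriction stated; separate cancer model |

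The mismatch is between the Rationale and the analysis. Aim 3 does not share the Rationale's limit.

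**2. What decides eligibility.** The cut-off is 1 or more in males and 2 or more in females, and female sex itself scores one point. One non-sex factor is therefore enough in either sex. Anyone with hypertension, diabetes, heart failure, prior stroke, vascular disease or age 65 or over is eligible.

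**3. Minimum crude artefact.** Assume uptake of 75% in all eligible patients, so no factor has any effect among them. Let u be uptake in ineligible patients, p the ineligible share and f the prevalence of the factor.
- With the factor, all are eligible: odds = 0.75/0.25 = 3.
- Without it, the ineligible share is s = p/(1 - f), which is at least p. Uptake = (1 - s) × 0.75 + s × u.
- Setting s = p gives the smallest possible artefact:
  - p = 6%, u = 50%: 0.94 × 0.75 + 0.06 × 0.50 = 0.735; odds 0.735/0.265 = 2.77; OR = 3/2.77 = 1.08.
  - p = 10%, u = 30%: 0.90 × 0.75 + 0.10 × 0.30 = 0.705; odds 0.705/0.295 = 2.39; OR = 3/2.39 = 1.26.

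A factor with no effect among eligible patients therefore has a crude OR of at least 1.08 to 1.26 under these inputs, whatever its prevalence.

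**4. Adjusted models.** Adjustment spreads the excess over the factors, so this step needs simulation.
- Uptake 75% against 30-50%, 6-10% ineligible: pooled adjusted ORs of about 1.0 to 1.5 for null factors (hypertension 1.17-1.50), against about 1.0 in eligible patients.
- Uptake 85% against 30%, five binary risk factors, 300,000 patients per scenario: pooled ORs of 1.25-1.76, 1.53-2.17 and 1.82-2.68 with 5%, 10% and 15% ineligible. Eligible-only ORs were 0.98-1.03.

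**5. Does adjusting for the score help?**
- Linear score: OR per point 1.09-1.27 in the first setting and 1.38-2.26 in the second, where the truth is 1.0. A straight line cannot absorb a threshold.
- Score plus an eligibility indicator: score OR 0.99-1.01 (second setting).
- Non-sex score entered as categories: component ORs return to about 1.0.

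**6. Other predictors.**
- True OR of 0.6 at age 85 or over: pooled adjusted OR with age bands 0.53-0.58, so not diluted. Only the crude OR (0.67-0.79) is diluted.
- A frailty-type driver with true OR 0.497 among the eligible: pooled 0.535-0.606 if it has no effect in ineligible patients, 0.53-0.55 if its effect there is the same, and 0.50-0.515 if it is stronger.

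The direction and size of any distortion depend on effects in ineligible patients, which the documents do not give.

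**The case against.** **The operative aim matches the analysis.** The Objectives and Aim 3 speak of prescribing in NVAF patients generally, and Aim 3 names stroke risk as a factor of interest. Aim 4 does say eligible, so the omission in Aim 3 may be deliberate. An association between stroke-risk factors and prescribing across all NVAF patients is then a valid answer to Aim 3. This stands: the all-NVAF model is legitimate as a description. It does not deliver what the Rationale promises.

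**Eligibility may enter the model as a covariate.** The models use the listed covariates, and the CHA2DS2-VASc entry contains both the score and the eligibility category. With an explicit category the artefact largely disappears. This stands in part: the protocol does not exclude such a term. But it commits to neither the category nor a form for the score, and the obvious default, a linear score, leaves the artefact in place.

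**The analysis set is inferred.** Data/statistical analysis does not name the set for the main model. All NVAF is the natural reading, given the Technical Summary and the absence of any restriction.

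**A stronger reading.** A reader might infer that pooling necessarily weakens real drivers of under-prescription, such as very old age, which the Study background names as an under-treated group. The documents do not support this. The planned analysis is multivariable, and step 6 shows no dilution of the age 85 or over effect once adjusted. Other predictors may move in either direction.

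**Conclusion.** The mismatch holds. The Rationale asks about eligible patients, while the main and cancer models are stated without that restriction and without a committed eligibility term. Non-prescription in ineligible patients is counted together with under-prescription, and eligibility-defining factors can appear as predictors when they have no effect among the eligible.

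The size rests wholly on assumption. With 6-10% ineligible and uptake of 75% against 30-50%, pooled ORs for null factors are about 1.0 to 1.5. Uptake of 85% against 30% makes them larger. If uptake did not differ by eligibility, this artefact would vanish.

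Severity is minor to moderate. Study type calls Phase 1 hypothesis generating, and the protocol already describes eligibility and stratifies trends by it. The point concerns the Phase 1 predictor models only and says nothing about how the Phase 2 cohort is chosen.

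**What to change.** In Data/statistical analysis, item 1, state that the under-prescription models, main and cancer, are fitted in patients classed as OAC eligible by the protocol's own CHA2DS2-VASc rule, and that these give the predictors of under-prescription. Keep the all-NVAF model, labelled as a description of prescribing, in line with the Objectives and Aim 3. Align the Technical Summary with both.

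If the sponsor prefers a single all-NVAF model, it should commit to an explicit eligibility term or a categorised non-sex score. If the eligible-only question is not intended, the Rationale should be reworded.

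The cost is one extra subset model for each analysis and a small loss of precision. If information scales with patient numbers, dropping 6-10% widens standard errors by a factor of 1/√0.94 = 1.03 to 1/√0.90 = 1.05. No new data are needed, because the score is already calculated for every patient.

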## Study background

In 2017, it was estimated that 1.4 million people in England have atrial fibrillation (AF), which is equal to 2.5% of the population. One of the main therapeutic goals in AF is to reduce the risk of thrombo-embolism and stroke, which can be achieved by using oral anticoagulants (OACs). Previous observational studies in the UK that used primary care data such as the CPRD, have found a steady increase in the prescribing of OACs throughout the past decade. This observed increase in OACs prescribing was further explained by the introduction and adoption of non-vitamin K oral anticoagulants (NOACs). This increasing uptake of OACs also corresponds to a change in the European Society of Cardiology (ESC) guidelines that recommended the treatment of moderate-risk to high risk AF patients with OACs rather than antiplatelets, as well as a change in the Quality and Outcome Framework (QOF) to incentivize prescribing of anticoagulants. However, despite this encouraging increase in OACs initiation in AF patients, evidence from an observational study using CPRD have showed that the proportion of patients not receiving any anticoagulation therapy from the year 2012 to 2016 remained the same, at around 15% of patients with non-valvular atrial fibrillation (NVAF).

The decision to start OAC therapy in AF patients mainly depends on balancing patient's risk for ischemic strokes against their risk for bleeding. Current guidelines recommend estimating stroke

risk in AF patients using the CHA2DS2-VASc score [congestive heart failure, hypertension, age 75 years, diabetes mellitus, prior stroke or transient ischemic attack or thromboembolism, vascular disease, age 65 to 74 years, and sex category]. OACs should be considered for patients with 1 or more non-sex CHA2DS2-VASc stroke risk factors. Patients with high-risk for stroke are those with CHA2DS2-VASc 2 in males or 3 in females. While bleeding risk assessment can be achieved by using HAS-BLED score [hypertension, abnormal kidney or liver function, stroke, history of bleeding, labile INR, elderly (> 65 years), and drugs/alcohol concomitantly]. However, a high bleeding risk score (HAS-BLED 3) should generally not lead to holding or not prescribing OACs. Rather, bleeding risk factors if modifiable should be identified and corrected such as hypertension, interacting medications, or labile international normalized ratio (INR) for patients on warfarin.

According to previous studies, elderly patients (>85 years) are less likely to be prescribed anticoagulation therapy, this observation is well documented in several studies, and is mainly attributed to the overestimation of bleeding risk. Moreover, elderly patients with high risk for stroke and those with coronary artery disease are more likely to be prescribed only one antiplatelet therapy, despite the 2016 ESC guidance which state that antiplatelet monotherapy should not be used for stroke prevention in AF patients. Observational studies showed that under prescribing of OACs in high-risk AF patients is associated with higher rates of stroke rates and death. OACs prescribing is largely based on physician's assessment of benefit (reducing stroke risk) versus risk (potential for bleeding), while considering many patients related factors. An example to this, is patients with AF and cancer since their risks of venous thromboembolism (VTE) and of non-cardio embolic stroke are higher than in the general population and may have to factor into the decision for some cancer subtypes, and also the bleeding risk is often much higher in patients with cancer due to coagulopathies, thrombocytopenia, anaemia that increase the propensity towards bleeding events. This illustrates the risk–treatment paradox previously reported in AF management that patients at higher risk of stroke and who are more likely to benefit from OACs are not receiving appropriate treatment, due to their bleeding risk. A comparative evaluation of physicians' decisions to prescribe OACs or not in high risk AF patients and their associated clinical outcomes could yield more informative, actionable conclusions if it provides a focused evaluation of patients characteristics and co-morbidities to identify the type of high-risk AF patients who would benefit from OACs without experiencing bleeding events.

Earlier studies have shown that anticoagulation therapy based on guideline risk stratifications is associated with a 60%–70% reduction in thromboembolic events and mortality. However, there is still room to improve risk stratification of patients with AF and anticoagulation. Recently, the Global Anticoagulant Registry in the FIELD-Atrial Fibrillation (GARFIELD-AF) model was developed and it allows the simultaneous prediction of stroke, bleeding, and mortality. This model is not a risk score that categorizes patients into risk groups, but instead it provides a risk prediction on a continuous scale. After external validation of the model in a Danish cohort, the GARFIELD-AF model was superior to CHA2DS2-VASc in predicting stroke/SE and comparable with HAS-BLED for predicting major bleeding. Due to the novelty of this risk prediction tool, further studies are needed to demonstrate its ability to accurately stratify AF patients based on their risk of stroke, bleeding, and mortality to promote informed decision-making to prescribe OACs.

Another contributing factor to the under-prescription of OACs in AF patients is history of major bleeding events during anticoagulation therapy. A meta-analysis of observational studies that evaluated the effect of reinitiating OACs on bleeding recurrence and thromboembolic events found a reduction in the risk of thromboembolism and all-cause mortality, without increasing recurrence of bleeding. Since randomized controlled trials (RCTs) that tested OACs, have excluded patients with previous intracranial haemorrhage (ICH), the timing to reinitiate OACs after ICH has not been systemically studied, and varies widely in observational studies from (72 hr to 30 weeks) reflecting lack of consensus. Moreover, of the available bleeding risk scores, the HAS-BLED score has been validated to predict ICH and recurrent ICH after first spontaneous ICH. However, it remains unclear if other risk assessment scores for stroke and bleeding hold similarly in these high-risk individuals and if they could be used to inform

decision-making for reinitiating OACs in these patients.

The available evidence presents several key aspects of AF management and the challenges associated with OACs prescribing in this population. There are still limitations in studies addressing the under-prescription of OACs in AF patients including patients with history of major bleeding events. In this proposed study we first aim to explore the incidence of NVAF in England to assess patients' characteristics and predictors of OACs prescribing in patients with NVAF in general and in those who have cancer as well. By examining the characteristics of NVAF patients who are less likely to receive a prescription for OACs, we will be able to further evaluate and compare the clinical outcomes of this sub-group of patients with a similar cohort of AF patients treated with OACs. Results could help determine in which AF patients at risk for stroke, OACs can be safely prescribed, taking in account patients' comorbidities, stroke and bleeding risk profiles. In addition to that, by looking separately at patients with history of major bleeding due to OACs, we

aim to evaluate the timing of reinitiating OACs and if stroke and bleeding risk assessment using the available risk prediction scores could be used to inform decision-making for reinitiating OACs in these patients, and their clinical outcomes.

